#### Study Objectives

The objectives of the pilot study were developed based on the formative stages of the protocol development by an expert panel that recognized the gaps that this study could fill. The primary objective is to determine the feasibility and acceptability of a pilot combination HIV prevention package specific for female and male youth (MP3 Youth) in Homa Bay County, Nyanza Province, Kenya. This will be determined by examining uptake and coverage of the intervention package among youth. The secondary objectives are (1) to examine adherence to HIV care including antiretroviral therapy (ART) among HIV-positive males and females 15 to 24 years of age; (2) to evaluate the feasibility of offering PrEP to high HIV risk out-of-school females 18 to 24 years of age and to contribute data to the current question of how best to initiate and support ongoing adherence for females using PrEP; (3) to assess the feasibility of delivering CCT to keep girls in school over the 12 months; and (4) to evaluate school attendance over 12 months of CCT cohort participants. For the logic model, see Multimedia Appendix 1.

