##### Conditional Cash Transfers

CCTs will be offered to girls enrolled in school (aged 15 to 24 years) and their families as part of the MP3 Youth package. The girls will be required to attend school at least 80% of the time in order for her and her family to receive the CCT. This will be measured by visiting the schools to check attendance. Much of the CCT evidence base has come from government sponsored programs, like the Mexico Opportunidades program designed as an anti-poverty program with positive impacts on social, economic, and health indicators [59]. CCT programs have demonstrated multiple impacts, such as keeping girls in school and measurable health benefits. The National Government of Kenya, in collaboration with the United Nations Children's Fund (UNICEF) and the World Bank, initiated a program in 2002 called the “Kenya *Cash Transfer Program* for Orphans and *Vulnerable Children.”* The program transferred USD $14 to $28 per month (depending on the number of vulnerable children in the household) to vulnerable youth in Kenya [60]. A recent study by Handa and colleagues (2014) evaluated the Kenya cash transfer program and found a 31% reduction in sexual debut [61]. The MP3 Youth pilot study protocol will offer critical information on the feasibility of keeping girls in school using CCT as an intervention.

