#### Cohort Follow-Up Schedules

Participants who attend the mobile MP3 Youth events will be enrolled into 4 cohorts which will be followed up for a period of 12 months via unstructured supplementary service data (USSD) and SMS text message (short message service, SMS) surveys and/or in-person computer-assisted personal interview (CAPI) surveys. The PrEP cohort will be followed up monthly for the first 6 months and every 3 months for the remaining 6 months in a mixture of in-person clinical visits and SMS and USSD surveys to facilitate adherence and conduct laboratory assessments (for HIV and pregnancy). The CCT cohort will be followed up every 3 months (0, 3, 6,9,12 months) for 12 months using an in-person CAPI and school registers checked for attendance. The HIV-positive cohort will also be followed up at intervals of 3 months via SMS and USSD surveys. A random subset of the HIV-negative youth who agree to be called in one year will receive a phone call to assess their HIV retesting behaviors and intentions. The HIV-positive cohort will undergo a clinical assessment at baseline and at month 12 (CD4 and viral load). The CCT cohort will undergo a clinical assessment at baseline and at month 12 (HIV testing and counseling and pregnancy testing). We will administer SMS and/or USSD and CAPI surveys to the cohorts to assess longitudinal self-reported behaviors. During all clinical/laboratory assessments, adverse events will be assessed.

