### Study Outcomes

Study outcomes were developed by an expert panel during the formative phases of protocol development to evaluate the objectives of the study and the aforementioned methods employed to deliver the interventions (see Multimedia Appendix 1). The primary and secondary outcomes of MP3 Youth are shown in Textbox 4.

Primary and secondary outcomes of the MP3 Youth protocol.OutcomesPrimary study outcomes (cross-sectional and cohort)Intervention uptake (acceptability) and coverage (feasibility)CoverageThe proportion of youth in the community who attend each mobile event (estimated from youth population denominator)EnrollmentThe number of participants who consent to being enrolled in the study during each mobile event.UptakeThe proportion of eligible participants who choose one or more components of their tailored combination package (including combinations of interventions components)Intervention acceptabilitySatisfaction with mobile event services (computer-assisted personal interview at exit from mobile event)Secondary study outcomesAdherence to medication (HIV-positive and pre-exposure prophylaxis cohort participants only)Adherence to once daily Truvada (pre-exposure prophylaxis, PrEP) among HIV-uninfected eligible females and patterns of adherence and sexual HIV acquisition risk exposure (PrEP cohort participants only).Measured by self-report, electronic medication vial, and clinical assessments: monthly for the first 6 months and every 3 months thereafter and dried blood spot for analysis of tenofovir disoproxil fumarate/emtricitabine and tenofovir diphosphate and emtricitabine triphosphate at month 2 and 9.Adherence to antiretroviral therapy (ART) (HIV-positive cohort participants only)Measured by quarter annual text messages/unstructured supplementary service data self-report at 0, 3, 6, 9, and 12 months.Point of care cluster of differentiation 4 (CD4) and baseline viral load by dried blood spot or plasma will be measured at mobile event baseline and repeated at 12 months.Feasibility of administering conditional cash transfer to keep girls in school over 12 months.Measured by school attendance (self-report and random checks for school attendance verification).

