#### Follow-Up Text Message and Unstructured Supplementary Service Data Survey

Using the EchoMobile platform, study staff will make SMS/USSD text contact using an agreed-upon code, to ensure the phone user is the study participant. Staff will then wirelessly transfer airtime, so the cohort participant can send surveys using SMS/USSD [63]. The SMS/USSD survey will be a brief 10-question survey tailored to the cohort population. The surveys will be short to reduce barriers to completion. The responses will be analyzed to assess change in behavior over time as a part of the longitudinal cohort.

The SMS survey will collect information that includes but is not limited to (1) sexual risk behaviors; (2) school attendance (for CCT cohort); (3) adherence barriers and facilitators (PrEP and HIV-positive cohort); and (4) status disclosure (HIV-positive cohort).

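### The CCT attendance outcome is defined as self-report with random checks, while two other sections take attendance from school visits and registers, and the source to be analysed is not settled

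*Protocol article*

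**What the plan says.** The protocol article describes the measurement of school attendance in the CCT cohort in three main places.

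- **Study Outcomes, Textbox 4.** CCT feasibility is a secondary outcome, "Measured by school attendance (self-report and random checks for school attendance verification".
- **Conditional Cash Transfers.** A girl is "required to attend school at least 80% of the time in order for her and her family to receive the CCT", and the next sentence reads "This will be measured by visiting the schools to check attendance". Self-report is not mentioned.
- **Cohort Follow-Up Schedules.** The CCT cohort is seen at 0, 3, 6, 9 and 12 months "using an in-person CAPI and school registers checked for attendance".

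The section on the follow-up text message survey also lists attendance among the items asked of the CCT cohort.

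Two secondary objectives depend on this measure. Under Study Objectives the third is "to assess the feasibility of delivering CCT to keep girls in school over the 12 months", and the fourth is to evaluate attendance in this cohort over the same period. The target cohort size is about 50 (Textbox 3).

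**The concern.** An outcome definition should identify the data that produce the analysed value. Here it names self-report first and gives verification only at random, although the same article plans visits to schools and checks of their registers. A reader who follows Textbox 4 and a reader who follows the follow-up schedule would build different datasets.

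The choice matters because attendance is a condition of receiving the transfer. Participants can be expected to know this, so self-reported attendance may lean upward. That would flatter the results for the third and fourth secondary objectives. A register kept by the school does not carry that particular bias.

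**Working it through.** **1. The plan's own figures.** Participants and Sample Size assumes at least 80% retention, and 50 × 0.80 = 40 evaluable CCT participants, as stated. It gives 80% power for a paired t test with 40 pairs at d = .45. The noncentral t calculation (39 degrees of freedom, noncentrality 0.45 × √40 = 2.85, two-sided 0.05 assumed) gives 79.3%, which agrees. The sample-size statement is sound and does not bear on measurement bias.

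**2. The descriptions side by side.**

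| Section | Source of attendance | Coverage |
|---|---|---|
| Study Outcomes, Textbox 4 | Self-report plus random checks | Share checked not stated |
| Conditional Cash Transfers | School visits | No subset named |
| Cohort Follow-Up Schedules | In-person interview plus school registers | 0, 3, 6, 9, 12 months; no subset named |
| Follow-up text message survey | Self-report | CCT cohort |

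No section says whether the random checks are the register checks, what share of girls or school days they cover, or which source prevails when they disagree.

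**3. Both ways of reconciling the text.**

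- If the random checks are the only school-based data, an unchecked girl contributes self-report alone. The register checks in the follow-up schedule are then described too broadly.
- If registers are checked for every girl every 3 months, a complete school-based source exists. Textbox 4 then names a weaker measure than the one collected.

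Either way, one of the sections needs rewording.

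**4. What the size depends on (illustration; every rate is assumed).** Let p be the true share of girls meeting the 80% condition, q the probability that a girl below it reports meeting it, and v the share of girls verified and corrected. No under-reporting is assumed. Then

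observed share = p + (1 − p) × q × (1 − v).

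With p = 0.70:

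| | q = 0.1 | q = 0.3 | q = 0.5 |
|---|---|---|---|
| v = 0.2 | 0.724 | 0.772 | 0.820 |
| v = 0.5 | 0.715 | 0.745 | 0.775 |
| v = 1 | 0.700 | 0.700 | 0.700 |

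For example, 0.70 + 0.30 × 0.5 × 0.8 = 0.820. The overstatement runs from zero to 12 percentage points. At v = 0.2 and q = 0.5 it would be 0.40 × 0.5 × 0.8 = 16 points for p = 0.60, and 0.20 × 0.5 × 0.8 = 8 points for p = 0.80. The documents fix none of p, q or v, so this shows what the answer depends on and is not an estimate. The one firm result is the last row: with every girl verified, over-reporting drops out.

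**The case against.** The strongest reply is that there may be no bias. The random checks could be the register checks under another name, or random in timing and not in coverage. If registers supply the analysed value, self-report does no harm. This is also a secondary outcome in a pilot that disclaims a definitive test, and the Results section plans to show attendance graphically. All of this is fair and limits the weight of the point. It does not remove the conflict, which lies in the stated outcome definition and is not a detail left to an unseen analysis plan.

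Several stronger readings are tempting, but the documents do not support them.

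- **Attendance will be overstated.** Only the possibility follows, and only if self-report is analysed.
- **Girls are paid for reporting high attendance.** Conditional Cash Transfers ties the condition to school visits, so a high self-report earns nothing under the stated rule. This weakens the motive to misreport, although a general wish to appear compliant may remain.
- **Most girls have self-report only.** No section gives the share checked.
- **A false rise appears once payments begin.** No payment start date is given, and the schedule includes month 0.
- **A bias of d = .45 would be declared a change about 79% of the time.** This is the plan's power with an assumed bias put in place of the effect. Over-reporting that is equal at both visits cancels in a paired comparison.
- **Delivery of the transfers goes unmeasured.** Textbox 4 does use attendance for feasibility, but delivery indicators may stand in the logic model or evaluation plan (Multimedia Appendices 1 and 2), which are not shown.

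**Conclusion.** The concern holds as a conflict between sections about the source of a stated secondary outcome, together with a definition that names a weaker measure although a school-based one is already planned. The conflict is certain on the text. The bias is conditional: attendance may be overstated if self-report is the analysed source, and its size cannot be derived from the documents. That conclusion assumes that girls know attendance is a condition of the programme and that registers are less open to this influence than their own reports. The sample-size figures are unaffected. The point bears on the third and fourth secondary objectives and not on the primary outcomes. It should be corrected.

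**What to change.** Reword the CCT entry in Textbox 4 to agree with Conditional Cash Transfers and Cohort Follow-Up Schedules. Make register-based percentage attendance, for every CCT participant at each 3-month assessment, the analysed attendance outcome. Keep self-report as descriptive or supportive only. If random checks are meant as something additional to the register checks, state what they add.

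The cost is small: a change of wording and complete register abstraction for about 50 girls at five time points, or about 250 abstractions (50 × 5) with full follow-up. Register checks for this cohort are already in the follow-up schedule.

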### Data Collection

This section of the protocol outlines the components that need to be included in order to collect and evaluate the cross-sectional and longitudinal data required to measure the pilot study outcomes. All MP3 Youth mobile event participants who are eligible, consent, and register for MP3 Youth will be required to complete a baseline behavioral CAPI survey and an exit acceptability interview. Participants who are eligible and enrolled in a sub-cohort will be required to complete SMS/USSD mobile phone surveys every month (PrEP cohort) or every 3 months (CCT and HIV-positive cohort). Participants in the PrEP cohort will be required to complete monthly clinical/laboratory visits for the first 6 months and every 3 months thereafter. The following sections describe the specific types of data that will be collected and the suggested data platforms to be implemented.

#### Behavioral Baseline Interview

The behavioral survey will be a staff-administered CAPI at the mobile events. For sensitive questions (which will be identified in the survey), youth will be instructed that they can tap on the answer with the tablet facing away from the interviewer and the answer will not be visible after entry; this incorporates elements of “ballot box response” or *audio computer-assisted self-interview* (ACASI) approaches while reducing issues around lack of literacy and unfamiliarity with tablet computers [62].

The CAPI will collect the following types of information, including but not limited to the types of services the participant is most interested in accessing: (1) basic demographic information, (2) sexual risk behaviors, (3) HIV risk behaviors, (4) attitudes and/or knowledge about HIV transmission and prevalence, (5) knowledge and acceptability of specific HIV prevention interventions, (6) knowledge and acceptability of family planning methods, and (7) attitudes towards the delivery of services (collected at the exit interview).

The CAPI will provide data that will lead to a better understanding of the combination HIV prevention interventions and prevention behaviors of youth. The responses will help determine the package of services for which the participant is eligible.

#### Follow-Up Text Message and Unstructured Supplementary Service Data Survey

Using the EchoMobile platform, study staff will make SMS/USSD text contact using an agreed-upon code, to ensure the phone user is the study participant. Staff will then wirelessly transfer airtime, so the cohort participant can send surveys using SMS/USSD [63]. The SMS/USSD survey will be a brief 10-question survey tailored to the cohort population. The surveys will be short to reduce barriers to completion. The responses will be analyzed to assess change in behavior over time as a part of the longitudinal cohort.

The SMS survey will collect information that includes but is not limited to (1) sexual risk behaviors; (2) school attendance (for CCT cohort); (3) adherence barriers and facilitators (PrEP and HIV-positive cohort); and (4) status disclosure (HIV-positive cohort).

#### Biometric Data Collection

Biometrics will be used to correctly identify participants, track repeat visits, and protect subject privacy and information. There will be a tablet connected via *Universal Serial Bus* (USB) to a biometric (fingerprint) scanner at the mobile events and during follow-up visits. This technology will be used to track uptake of services and to exclude individuals who try to enroll multiple times. The fingerprint software will translate a fingerprint into a code containing numbers and letters; no image of the fingerprint will be stored. In testing this procedure, we will take several measurements of correctly positioned clean fingers to ensure accurate measurement and re-measurement. The code will not be a personal identifier and it will not be possible to use it to recreate a fingerprint. These codes will be stored separately from other data. This technology has been used successfully in other projects in Kenya [64].

#### Biomedical Data Collection

Urine specimen will be collected for pregnancy testing for women with reproductive capacity and for dipstick analysis of protein and glucose levels (PrEP cohort only). In the PrEP cohort only, blood specimens will be collected for (1) HIV rapid testing, with confirmatory testing if one or both tests are reactive; (2) complete blood count (CBC); (3) serum creatinine (for estimated creatinine clearance); (4) serum phosphate; (5) aspartate transaminase (AST)/alanine transaminase (AST) ratios; (6) hepatitis B surface antigen (HepBsAg) (ineligible for PrEP if positive); (7) hepatitis B surfance antibody (HepBsAb) and hepatitis B Core antibody (HepBCore Ab) testing (if HepBsAg is negative); and (8) DBS for study drug levels as a measure of adherence. Blood specimens will also be collected to determine the CD4 cell count in any participant with confirmed HIV infection and viral load testing.

#### Implication of Pilot Study Results

Data from Aim 3 (the pilot study), the mathematical modeling sensitivity analyses, and the population impact projections will help establish the acceptability, feasibility, potential synergies or antagonisms, safety, and potential efficacy of the package before moving to a larger-scale evaluation phase IV study design (Aim 4).

### Aim 4: Combination Prevention Effectiveness Study Design

Using lessons from Aims 1 to 3 of the protocol, we present a preliminary outline for the design of a future effectiveness trial of the MP3 Youth package. The objective of the effectiveness trial will be similar to the pilot, but the trial will focus on effectiveness and not on feasibility.

Arguably, insufficient attention has been given to moving phase III efficacy trial interventions to phase IV effectiveness designs applied in heterogeneous real-world settings [65]. Several study designs can be considered to evaluate actual population-level impact of gender-specific combination prevention intervention packages for youth (Table 1), including cluster randomized controlled trials (cRCTs) using parallel or stepped wedge (ie, staggered) assignment. The advantage of cRCTs over individually randomized controlled trials (iRCTs) is that the former allows evaluation of the total effect of a combination package, especially if the sum of the intervention package components is greater than its parts [66]. They would also allow assessment of targeted interventions to subpopulations (eg, in the case of MP3 Youth males vs females or pregnant vs non-pregnant females) while the impact would be measured on the whole community. The feasibility of tracking an HIV incidence outcome for either an iRCT or cRCT would depend on development of improved cross-sectional HIV incidence assays. It would also depend on the expected HIV incidence in the control arm and likely HIV-incidence reduction effect size in the combination arm.

**Table 5 table1:** Potential designs for a testable combination HIV prevention intervention study protocol.

Study design	Advantages	Disadvantages	Considerations
iRCT^a^	Rigorous control of confounders	Can’t evaluate population HIV impact	Need high incidence; control condition can weaken intervention detection
cRCT^b^	Rigorous, can assess impact beyond individual	Cost, complexity	Unit of randomization, and number of clusters and individuals within clusters
cRCT stepped wedge randomization	Easier to add interventions, once shown effective	Implementation delays can reduce effectiveness and power	Appropriate when logistically difficult to roll-out prevention service all at once
Program demonstration	Could be done in large scale in existing programs	Less rigorous, results can be inconclusive	Selection/matching of intervention and control communities; incidence measures

^a^iRCT: individually randomized controlled trial.

^b^cRCT: cluster randomized controlled trial.

We can use findings from Aims 1 to 3 to inform choice of (1) study design (including standard of care elements); (2) high HIV incidence setting (in Kenya or elsewhere) with sufficient HIV events expected; and (3) HIV incidence measurement for a full-scale evaluation of a gender-specific youth combination prevention package. Other key considerations that can be reviewed include what the trial unit of randomization should be, standard of care and/or comparator, timeframe expected for seeing an intervention effect, length of follow-up period needed to observe sufficient number of new HIV infections, sample size, participant inclusion/exclusion criteria, and how best to engage active and ongoing community involvement in large-scale trial design and conduct. Safety considerations and adverse event tracking must be delineated. We must also consider broader issues of the logistics of program coverage, cost-effectiveness, and sustainability beyond the study period. After compiling the possible options, we will collaborate with our research team to review our recommended study elements and make final trial design recommendations.

### Human Participants

The MP3 Youth study has institutional review board (IRB) approval from Kenyatta National Hospital/University of Nairobi-Ethics and Research Committee (KNH-ERC) and from New York University’s governing IRB, University Committee on Activities Involving Human Subject (UCAIHS).

